## Abstract

Coronary heart disease is one of the main causes of morbimortality around the world. Patients that survive a coronary event suffer a high risk of readmission, relapse and mortality, attributed to the sub-optimal control of cardiovascular risk factors (CVRF), which highlights the need to improve secondary prevention strategies aimed at improving their lifestyle and adherence to treatment. Through a randomized controlled clinical trial, this study aims to evaluate the effect of an intervention involving an online health application supported by a mobile telephone or tablet (mHealth) on lifestyle (diet, physical activity, and tobacco consumption) and treatment adherence among people with coronary heart disease after percutaneous coronary intervention. The sample will comprise 240 subjects (120 in each arm: intervention and usual care). They are assessed immediately and nine months after their hospital discharge about sociodemographic, clinical, CVRF, lifestyle, and treatment adherence characteristics. The educative intervention, involving a follow-up and self-monitoring, will be performed using an online mHealth tool consisting of an application for mobile phones and tablets. The quantitative primary outcomes from the two groups will be compared using an analysis of covariance (ANCOVA) adjusted for age and gender. A multivariate analysis will be performed to examine the association of the intervention with lifestyle habits, the control of CVRFs, and outcomes after discharge in terms of the use of health services, emergency visits, cardiovascular events and readmissions.

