### 3.1. Variables Collected in the Initial and Final Evaluations

All the participants are evaluated at the beginning and end of the study though an interview, checking the information given against their electronic medical records. During hospitalization, after the PCI, an assessment is performed of sociodemographic characteristics, educational level, alcohol intake, tobacco consumption, and clinical situation (history of diabetes mellitus and its complications, high blood pressure, hyperlipidemia, previous cardiovascular events, number of stents implanted, Euroscore II scale classification of the left ventricular ejection fraction (LVEF)) [43]. Body weight, height (to calculate BMI), waist circumference [42], and systolic and diastolic blood pressure (mm Hg) will be measured. An examination will be performed of plasma concentrations of LDL cholesterol (mg/dL), high-density lipoprotein (HDL) cholesterol (mg/dL), and baseline blood glucose and glycosylated hemoglobin (HbA1c) in patients with diabetes corresponding to levels in analyses performed before the intervention and after the final evaluation. Tobacco consumption will be assessed by the self-reported number of cigarettes per day and the Fagerstrom nicotine dependence test. [44,45] Stopping smoking will be self-reported and confirmed by a concentration of carbon monoxide in exhaled air of fewer than six parts per million measured with a co-oximeter CO CHECK PRO (MD Diagnostics LTD) at the beginning and end of the study. To evaluate dietary intake patterns, validated questionnaires will be used for assessing adherence to the Mediterranean diet and the frequency with which foods are consumed [33,34]. To convert the food consumed into kilocalories and nutrients, Spanish food composition tables will be used [46]. Physical activity will be evaluated using the validated Spanish version of the Minnesota physical activity questionnaire (MET min/week) [35,36]. The time (minutes/day) for sedentary activity and sleep will also be recorded. Treatment adherence will be evaluated using the Morisky–Green test [47]. Knowledge of coronary disease, CVRFs, and a healthy lifestyle will be examined using a validated questionnaire [48]. An OMS questionnaire will be used to study levels of anxiety and depression [49], quality of life [50], and well-being [51].

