#### 3.2.1. Primary Outcome Variables

The primary outcome measures after nine months in both groups will be changes in behavior relating to 1. Healthy diet: Adherence to the Mediterranean diet and average intake of each food group. 2. Level of physical activity (MET) and the number of steps per day, and a less sedentary lifestyle. 3. Smokers stop smoking. 4. Treatment Adherence. 5. Knowledge acquired. 6. Usability and satisfaction with the application.

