### 3.3. Statistical Analysis

The principles of intention-to-treat analysis will be followed. The differences between patients who gave up the app and those who were able to utilize it will also be examined by analyzing the outcome variables from the electronic medical record. A descriptive statistical analysis will be performed (mean, standard deviation, 95% confidence interval, frequencies, and percentages). For the comparison of means, the Student’s t-test will be used (normal distribution variables) and the Mann–Whitney U test (if the variables are non-normally distributed). The Chi-squared/Fisher test will be used for the comparison of proportions. The relative risks and 95% confidence intervals will be computed. The quantitative primary outcomes from the two groups will be compared using an analysis of covariance adjusted for age and gender. A sensitivity analysis will also be performed regarding the baseline characteristics of the participants in both groups and missing data. A multivariate analysis will be performed to examine the association of the intervention with lifestyle habits, control of the CVRFs and evolution after discharge regarding cardiovascular events, the use of health services, emergency visits, and readmissions using Kaplan–Meier survival analysis. A two-tailed *p*-value < 0.05 will be considered statistically significant. The SPSS v.24.0 software will be used. 24.0. The researchers analyzing the results will be blinded to the allocation of the participants.

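### If treatment adherence is analysed as yes/no, its only named test is an unadjusted chi-squared/Fisher test that leaves the collected baseline adherence unused; the power lost is modest and may be near zero

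*Protocol article*

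**What the plan says.** The Abstract specifies one adjusted between-arm comparison: "The quantitative primary outcomes from the two groups will be compared using an analysis of covariance (ANCOVA) adjusted for age and gender". Section 3.3 repeats it: "The quantitative primary outcomes from the two groups will be compared using an analysis of covariance adjusted for age and gender". For binary outcomes section 3.3 says "The Chi-squared/Fisher test will be used for the comparison of proportions" and "The relative risks and 95% confidence intervals will be computed". No covariates are attached to either sentence.

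Section 3.2.1 includes among the primary outcomes "3. Smokers stop smoking. 4. Treatment Adherence". Section 3.1 says "Treatment adherence will be evaluated using the Morisky–Green test" and places this among the variables assessed at both the initial and the final evaluation, so a baseline value will exist. It does not say whether the result is analysed as a category or as a score.

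Two further analyses in section 3.3 bear on the point. One is a sensitivity analysis concerning baseline characteristics and missing data, with no form given. The other is this: "A multivariate analysis will be performed to examine the association of the intervention with lifestyle habits, control of the CVRFs and evolution after discharge". Treatment adherence is not in that list, and the Abstract names it separately from lifestyle in its statement of aims: "lifestyle (diet, physical activity, and tobacco consumption) and treatment adherence".

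**The concern.** Treatment adherence is one half of the trial's stated aim. If it is scored yes/no, it falls under the chi-squared/Fisher sentence and not under the ANCOVA. The between-arm comparison then makes no use of whether the patient was adherent at baseline, although that is recorded for everyone and may predict adherence at nine months. Nothing else in section 3.3 clearly brings adherence into an adjusted model.

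What is at stake is precision, not validity. In a 1:1 randomised trial the unadjusted test keeps its type I error and the relative risk is not biased. It may simply be less sensitive than the collected data allow.

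**Working it through.** **The plan's own figure.** There is none to reproduce. Section 2.4 gives planning values for diet, food groups, physical activity and smoking, but none for treatment adherence. The inputs below are therefore assumptions, apart from the first.

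**Inputs**
- Analysed patients per arm: 120 × (1 − 0.20) = 96 (enrolment and loss to follow-up from section 2.4).
- Usual-care adherence at nine months: 57%. The Introduction reports that 30% stop treatment by three months and 50% by one year. Linear interpolation gives 70% − (70% − 50%) × 6/9 = 56.7%. Those figures describe stopping treatment, not a Morisky–Green result, so this is only a rough stand-in.
- Intervention adherence: 72%, an assumed 15-point effect.
- Baseline adherence: 50%, assumed.
- Correlation (phi) between baseline and follow-up adherence within arm: not given, so varied from 0 to 0.47.
- Two-sided 5% level (section 3.3).

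**Unadjusted power, by formula**
- Mean proportion: (0.57 + 0.72)/2 = 0.645.
- Standard error under no difference: √(2 × 0.645 × 0.355/96) = 0.0691.
- Standard error under the alternative: √((0.57 × 0.43 + 0.72 × 0.28)/96) = 0.0682.
- Power = Φ((0.15 − 1.96 × 0.0691)/0.0682) = Φ(0.21) ≈ 58%.

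**Effect of using baseline adherence.** Adjustment reduces the residual variance by a factor of roughly 1 − phi². The simulated comparison was an unadjusted chi-squared test against a test stratified by, or a logistic model containing, a two-level baseline indicator:

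| phi | 1 − phi² | Unadjusted power | Power using baseline |
|---|---|---|---|
| 0 | 1.00 | about 58% | 58% |
| 0.20 | 0.96 | about 58% | 60% |
| 0.33 | 0.89 | about 58% | 63% |
| 0.47 | 0.78 | about 58% | 69% |

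Type I error stayed near 5% for both tests.

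**Sensitivity to other rates** (100 per arm, 50% adherent at baseline)
- 50% vs 70%: about 83% unadjusted. Adjusted, 84% at phi 0, 86% at 0.3 and 92% at 0.5.
- 50% vs 65%: 57–60% unadjusted. Adjusted, 58% at phi 0, 61% at 0.3 and 69% at 0.5.

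The gain is about 3 points at phi 0.3 in both cases and about 10 points at phi 0.5. These runs adjust for baseline adherence only; a model that also contains age and gender was not simulated.

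**Smoking, as a boundary check.** Take 96 per arm, 21% baseline smokers (section 2.4), and assume 30% vs 60% quitting and 2% relapse or uptake in non-smokers. A chi-squared test of cessation among the roughly 0.21 × 96 ≈ 20 smokers per arm has about 49% power. Comparing smoking prevalence in all patients has about 25% unadjusted and about 38% when stratified by baseline smoking. The planned test on the outcome listed in section 3.2.1 therefore already does better than an adjusted prevalence comparison.

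**The case against.** The strongest case against is that nothing here is wrong. A chi-squared/Fisher test with relative risks is a legitimate primary analysis after randomisation, and an article may leave the details of a model to the analysis plan. The first part stands and limits the point to efficiency. The second stands only in part, because section 3.3 does not leave the test open: it names an unadjusted one.

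The adherence case also rests on assumptions. Morisky–Green may be analysed as a score, in which case the ANCOVA sentence could apply. Baseline is recorded in hospital after the coronary procedure, while the outcome concerns medication after discharge, so a low correlation is plausible. Both objections stand, and they are why the gain is given as a range starting at zero.

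A reader might infer three stronger claims that the article does not support:
- **That smoking cessation also discards baseline status.** The listed outcome is cessation among smokers, so baseline smoking defines the denominator and is constant within it. Adjusting for baseline smoking matters only if smoking is compared as prevalence in all patients, the basis that section 2.4 suggests.
- **That binary outcomes receive no adjusted analysis at all.** The multivariate analysis covers lifestyle habits, which in the Abstract include tobacco, and a baseline-characteristics sensitivity analysis is planned. Neither is specified, and neither names treatment adherence.
- **That quantitative outcomes use their baseline values while binary ones do not.** The ANCOVA as stated adjusts for age and gender only. Extending that same rule to adherence would not bring in baseline adherence; it has to be added explicitly.

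**Conclusion.** The point holds for treatment adherence, on the condition that the Morisky–Green result is analysed as yes/no. The only test then named for a primary outcome is unadjusted and leaves a collected baseline measurement unused. Under the assumed 57% vs 72% with 96 per arm, the power forgone runs from nothing at phi 0 to about 11 points (58% to 69%) at phi 0.47. The correlation is not in the article and the rates are assumed, so no single figure for the loss can be claimed. This is an inexpensive improvement in efficiency, not the correction of an invalid analysis, and it does not extend to smoking cessation among baseline smokers.

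**What to change.** In section 3.3:
- State whether the Morisky–Green result is analysed as a category or as a score.
- If as a category, make the primary between-arm adherence comparison a logistic or modified Poisson regression on arm, age, gender and baseline adherence. Report a standardised risk ratio or risk difference with its 95% confidence interval.
- Say how patients with no treatment before admission are coded at baseline.
- Keep chi-squared/Fisher as a descriptive comparison.
- For smoking, add baseline smoking as a covariate only if the comparison is prevalence in all patients.

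The cost is a few sentences of wording. No new data are needed, and in the simulations adjustment cost essentially no power when baseline was uninformative. The change should be fixed before any outcome data are compared by arm; the article reports 95 patients recruited so far.

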## 1. Introduction

Coronary heart disease is one of the main causes of morbimortality around the world [1]. Although progress has been made in the treatment of cardiovascular risk factors (CVRF) such as hypolipidemic and antihypertensive drugs, the results have fallen short of expectations. This is partly a result of the increased prevalence of obesity and type-2 diabetes mellitus, although the ageing population is also partly to blame [2]. Coronary interventions with stenting have achieved excellent clinical outcomes among these patients. However, although this procedure restores blood flow to the heart, it does not protect the myocardium against the onset of further coronary obstructions [3,4].

Thus, a high risk of readmission, relapse, and mortality has been seen to exist in the years following a myocardial infarction due to inadequate control of cardiovascular risk factors, highlighting the need to improve secondary prevention strategies [5,6]. Consequently, the first step is to educate patients about lifestyle habits and how to control CVRFs, in addition to conducting cardiac rehabilitation and complying with suitable pharmacological treatment.

Secondary prevention strategies aimed at changing these lifestyle habits and changing CVRFs are cost-effective thanks to the savings in both medication and future catheterization interventions or surgery [7,8,9]. However, a large number of patients do not comply with lifestyle recommendations or do not take their medication appropriately after a cardiovascular event, which results in them not reaching their treatment objectives. Among these patients, 30% stop the treatment three months after the first heart attack, while 50% abandon it after a year [10,11]. For this reason, patients need help and information about making changes in their lifestyles and adhering to their pharmacological treatment. This advice should be provided by the medical team (doctors and nurses) in the hospital and given before patients are discharged, as recommended in clinical practice guidelines [10].

In turn, patients must have the knowledge, means, and institutional support to take care of their health. However, they often encounter difficulties understanding the information they receive because the time short allotted for appointments makes detailed explanations impossible, which has been recognized as one of the hurdles in understanding the risk they are facing [12].

It has been shown that intensive, structured interventions lead to positive changes in the lifestyle of patients with coronary heart disease. They achieve improvements in CVRFs, contribute to the prevention of events and reduce hospital admissions [10,13,14,15,16], even being more successful in secondary than in primary prevention [12,17].

The development of new online communication channels between health professionals and patients may help to improve the care given by the latter. This technology also makes patients more self-reliant in the monitoring of their illness, allowing them to play a more active role while enabling health professionals to obtain more information about the health status of their patients.

Currently, over 75% of the world’s population has a mobile telephone with internet access, and over 57% of homes have an internet connection. In Europe, those figures reach 99% and 86% respectively [18,19].

These data suggest that smartphones have become a part of many aspects of day-to-day life and that they are potentially useful tools for managing health and lifestyle, and can be incorporated into communication between health professionals and patients.

Accordingly, the American Health Association issued a scientific statement in 2015 urging for an increase in research to assess the viability and efficacy of mobile health applications in the prevention of cardiovascular disease (CVD) [20].

Several clinical trials with varying intensity, duration, interventional components and contexts have analyzed the efficacy of using mobile devices as a tool for enhancing health-promoting habits and encouraging adherence to treatment in different populations. The mActive clinical trial evaluated the capacity of a system of automated and personalized text messages to increase physical activity, reporting a 25% increase in physical activity among the study group and concluding that text messaging acted as a driver of lifestyle changes. However, the limitations of this study were its short duration and the limited sample size [21].

In turn, the TEXT ME clinical trial studied the use of sending text messages to patients with coronary heart disease over six months, and found improvements in the intervention group regarding the CVRF objectives recommended in guidelines [22]. Other studies have also attempted to determine the effect of text messages on adherence to medication among coronary heart disease patients, but with differing results and limited effect sizes [23,24].

More recent clinical trials have studied the use of mobile phone applications as potential tools for improving adherence to treatment, the control of CVRFs, and the clinical outcomes of patients that suffered from a coronary event [25,26,27]. These patients are generally overwhelmed by a series of complex prescriptions for medicines, diets, and other advice.

In this sense, several systematic reviews and meta-analyses have analyzed the effectiveness of mHealth interventions in improving treatment adherence and self-monitoring of cardiovascular risk factors in patients with heart disease, although disparate results were found [28,29,30]. However, although a range of behaviors can be modified using mobile applications, there is a need for more studies of longer duration to provide evidence about the efficacy. These should better describe the characteristics of the intervention and the patients to fill the existing knowledge gap. In addition to extending the study for nine months, the present project involves a structured, systematic methodology that will enable the results to be compared with other international studies. [31].

This study aims to evaluate, through use of a randomized controlled clinical trial (RCT), the effect of an intervention involving a mobile health application on the lifestyle and treatment adherence of people with coronary heart disease after percutaneous coronary intervention in terms of:Improvements in the pattern of diet and food consumption, physical activity and smoking habits.The objective measures of cardiovascular risk such as body mass index (BMI), waist circumference, blood pressure, and low-density lipoprotein (LDL) cholesterol.Acquiring knowledge about cardiovascular diseases (CVD), the risk factors, and a healthy lifestyle.The patients’ level of anxiety, quality of life, and well-being.The participants’ commitment to using the application and the level of self-monitoring of CVRFs.The participants’ satisfaction regarding the usability of the application.Use of health services, emergency visits, and readmissions of the participants throughout the study.

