#### 3.2.2. Secondary Outcome Variables

The secondary outcome variables will be 1. BMI. 2. Waist circumference. 3. Blood pressure. 4. Total cholesterol and LDL cholesterol. 5. Capillary blood glucose, and blood glucose, and HbA1c in the patients with diabetes. 6. Cardiovascular events, use of health services, emergency visits, and readmissions throughout of the study.

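### Section 3.3 names no baseline-adjusted analysis for the continuous secondary outcomes (BMI, waist, blood pressure, LDL), although they are measured at both evaluations; the cost is precision, not validity

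*Protocol article*

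**What the plan says.** All references are to the protocol article.

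- **Aim (Introduction).** One aim concerns "The objective measures of cardiovascular risk such as body mass index (BMI), waist circumference, blood pressure, and low-density lipoprotein (LDL) cholesterol".
- **Tier (3.2.2).** "The secondary outcome variables will be 1. BMI. 2. Waist circumference. 3. Blood pressure. 4. Total cholesterol and LDL cholesterol". The list gives variable names only. It does not say whether the final value or the change is to be compared.
- **Measurement (3.1).** "Body weight, height (to calculate BMI), waist circumference [42], and systolic and diastolic blood pressure (mm Hg) will be measured". Participants are evaluated at the start and end of the study, and the laboratory values come from before the intervention and after the final evaluation. An initial value is therefore planned in both arms.
- **Role (2.2).** Participants cannot be blinded, so objective clinical variables are one of the stated means of limiting bias.
- **Methods (3.3).** Three sentences could bear on these outcomes:
  - "The quantitative primary outcomes from the two groups will be compared using an analysis of covariance adjusted for age and gender".
  - For comparing means, Student's "t-test will be used (normal distribution variables"), with Mann–Whitney for non-normal variables. This rule is assigned to no outcome tier.
  - "A multivariate analysis will be performed to examine the association of the intervention with lifestyle habits, control of the CVRFs and evolution after discharge". That sentence ends by naming Kaplan–Meier survival analysis as the method. The Abstract has a parallel sentence without Kaplan–Meier: "A multivariate analysis will be performed to examine the association of the intervention with lifestyle habits, the control of CVRFs, and outcomes after discharge".
- **Sensitivity (3.3).** A sensitivity analysis on baseline characteristics and missing data is also planned.

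**The concern.** BMI, waist, blood pressure and LDL at nine months depend in part on where each patient started. An analysis that includes the initial value removes that part of the between-patient variance and corrects for chance differences between arms at baseline. Section 3.3 does not say that this will be done for any of these outcomes.

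These are also the outcomes least open to self-report bias in a trial whose participants know their allocation. Section 2.4 does not size the trial for them, so their precision depends on the analysis chosen. If the main comparison is unadjusted, a modest real effect on a risk factor could be reported as inconclusive when the data already collected would have supported a clearer answer. Leaving the method open also allows final-value, change and adjusted analyses to be chosen after the results are seen.

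**Working it through.** **1. Which stated method fits a continuous secondary outcome?**

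- ANCOVA: named for quantitative primary outcomes, with age and gender as the only covariates. Extending it as written to secondary outcomes would still not bring in their initial values.
- t-test or Mann–Whitney: fits, but is unadjusted.
- Multivariate analysis: covers risk-factor control, but gives no covariates and no model type. Its one named method, Kaplan–Meier, estimates time-to-event curves and cannot analyse a 36-week BMI, waist, pressure or LDL value.

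So the only named method that suits these outcomes is unadjusted.

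**2. Inputs.** From the article: 120 per arm, 20% loss and 90% power (2.4), and two-sided 0.05 (3.3). Evaluable patients: 120 × (1 − 0.20) = 96 per arm. The correlation r between initial and 36-week values is not given, so 0.5, 0.7 and 0.9 are assumptions. Equal variance at both times is assumed, and the few degrees of freedom used by covariates are ignored.

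**3. The plan's own figure.** Section 2.4 states 100 per group for the behavioural outcomes at d = 0.5. The normal approximation gives 2 × 3.242² / 0.5² = 84.1, so 85 per group. The figure of 100 is not reproduced, but nothing here depends on it, because no secondary outcome enters that calculation.

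**4. Detectable difference at 90% power, in SD units of the outcome.**

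- Final value, unadjusted: (1.960 + 1.282) × √(2/96) = 3.242 × 0.1443 = 0.468.
- Change from the initial value, unadjusted: 0.468 × √(2(1 − r)).
- ANCOVA with the initial value: 0.468 × √(1 − r²).

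| Assumed r | Final value | Change | ANCOVA with initial value |
|---|---|---|---|
| 0.5 | 0.47 | 0.47 | 0.41 |
| 0.7 | 0.47 | 0.36 | 0.33 |
| 0.9 | 0.47 | 0.21 | 0.20 |

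**5. The same in power, for an assumed effect of 0.3 SD and 96 per arm.**

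| Assumed r | Final value | Change | ANCOVA with initial value |
|---|---|---|---|
| 0.3 | 54.7% | 41.9% | 58.7% |
| 0.5 | 54.7% | 54.7% | 67.0% |
| 0.7 | 54.7% | 76.5% | 82.9% |

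Change does worse than the final value when r is below 0.5 and better above it. ANCOVA is the most precise of the three at every r shown, so r need not be known to choose it. For an effect of 0.5 SD, the unadjusted final-value test already has 93.4% power and the gain hardly matters.

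**6. Chance imbalance.** With 120 per arm, the 95% range of the baseline difference between arms is ±1.96 × √(2/120) = ±0.25 SD. An unadjusted comparison of final values carries a fraction r of any such difference into the result: up to about 0.7 × 0.25 = 0.18 SD at r = 0.7.

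**The case against.** The strongest reply is that the document does plan more than a t-test. Section 3.3 and the Abstract both announce a multivariate analysis that includes control of the risk factors. Kaplan–Meier may be meant only for the last items in that list (events, emergency visits and readmissions), and the Abstract does not attach it at all. Section 3.3 also plans a sensitivity analysis on baseline characteristics. The article is condensed, and covariates for secondary outcomes are commonly set in a full protocol or SAP that is not shown.

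Much of this stands, and it rules out three stronger readings that a reader might infer:

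- **That no covariate model is planned for these outcomes.** The multivariate analysis is planned; it is simply unspecified.
- **That they will be analysed by plain t-tests only.** The rule for means is general and is not assigned to the secondary tier.
- **That final levels rather than changes will be compared.** Section 3.2.2 lists variables and is silent on the metric. The choice matters for the size of the problem, because at r = 0.9 a t-test on change (0.21 SD) is almost as good as ANCOVA (0.20 SD).

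What does not stand is the view that this is mere silence left to another document. Section 3.3 assigns ANCOVA to one tier, gives an unadjusted rule for means, and puts risk-factor control in a sentence whose only named method cannot analyse it. The Abstract's version adds no covariate or model. A sensitivity analysis on baseline characteristics is not the main comparison and does not name these outcomes.

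**Conclusion.** The point holds as a gap in specification with a cost in efficiency. Section 3.3 names no baseline-adjusted analysis for BMI, waist, blood pressure or LDL, although the initial values are to be collected. An unadjusted comparison remains valid under randomisation, so type I error is not at issue. What is lost is precision and protection against chance imbalance.

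The size depends on two things that the article does not give: the correlation and the comparator. Against final values, the detectable difference falls from 0.47 SD to 0.41 or 0.33 SD at assumed r = 0.5 or 0.7. Against change, it falls from 0.47 to 0.41 SD and from 0.36 to 0.33 SD, and at r = 0.9 the gain almost vanishes. The gain matters mainly for effects smaller than the 0.5 SD used to size the behavioural outcomes.

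The primary ANCOVA has the same gap, since it too names no initial value. Correcting it alone would leave the secondary outcomes uncovered.

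**What to change.** In section 3.3:

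1. State that each continuous secondary outcome measured at both evaluations (BMI, waist, systolic and diastolic pressure, LDL, and blood glucose and HbA1c in patients with diabetes) is compared by ANCOVA on the 36-week value, with arm, the same variable's initial value, age and gender as covariates.
2. Keep the t-test and Mann–Whitney comparisons of these outcomes as descriptive.
3. Confine Kaplan–Meier to the time-to-event outcomes.

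Capillary glucose falls outside item 1, because section 3.2 has it recorded through the application in the intervention group only.

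The cost is a wording change, with no new data, visits or patients. Section 2.5 reports 95 of the planned 240 patients recruited at the time of writing. The change should be recorded before the outcome data are analysed by arm, so that it counts as prespecified.
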